### **5.3. Statistical Analysis**

Descriptive statistics for all demographic variables and clinical measures will be calculated for each group. To determine if there are statistically significant differences between the 2 groups at baseline, t-tests will be calculated for continuous measures and chi squares will be calculated for categorical measures. Regardless of any differences, baseline values for key outcome variables will be included as covariates in the main assessments of the effect of diet in the multivariate analysis of covariance. An alpha of 0.05 will be used for all statistical tests.

For nutrient intake and physical measures, descriptive statistics (means, standard deviations, tests for normality) will be calculated. If data are normally distributed, parametric tests for significant effects will be used; for non-normally distributed variables, non-parametric tests will be used.

The initial test of the hypotheses will be examined by performing t-tests for independent samples on the difference score denoting the change from baseline to the reporting period. For missing data in a reporting period, values from the previous period will be brought forward. For body weight, drop-outs will be considered to have returned to baseline weights.

**5.4. Assessment of Diet Adherence.** Diet-and-supplement group participants will be described as adherent or non-adherent based on whether they met the following criteria: absence of proscribed foods reported on 24-hour recalls and diet records, saturated fat <5% and total fat <25% of energy, and average daily cholesterol intake <50 mg on 3-day dietary records.

For drop-out rates, we will determine if there are between-group differences, using chi-square.

**5.5. Assessment of Medication use.** Any changes to lipid-lowering medications will be classified as a net increase, net decrease, or mixed (changes in opposing directions for 2 or more medications). Using chi-square, we will determine whether there are differences in medication changes between the 2 groups.

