### **1. SPECIFIC AIMS AND OVERVIEW**

#### **1.1. Specific Aims**

**Specific Aim 1.** This study tests the hypothesis that weight changes associated with a low-fat plant-based diet are, in part, the result of increased postprandial metabolism (thermic effect of food).

**Specific Aim 2.** This study tests the hypothesis that increased postprandial metabolism in response to a diet intervention is the result of increased insulin sensitivity.

**Specific Aim 3.** This study conducts a pilot substudy to test the hypothesis that changes in insulin sensitivity observed in response to a diet intervention correlate with changes in intramyocellular and/or intrahepatocellular lipid.

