#### **1.2. Protocol Overview**

In a 16-week trial, overweight adults will be randomly assigned to two groups. Changes in insulin sensitivity, postprandial metabolism, and body weight will be the primary dependent variables.

The Diet Group will be asked to follow a low-fat, vegan diet and will receive weekly classes and support.

The Control Group will be asked to make no changes in diet or exercise for 16 weeks, but will be instructed in the intervention diet at the study's conclusion.

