The study does not seek to separate the effects of the diet from those of regular group support. Rather, group support is a means of facilitating adherence. It should also be emphasized that the goal of this study is not to construct an intervention diet that is isocaloric compared with diets followed by the Control Group participants. Because the intervention diet is low in fat and high in fiber, self-selected energy intake is likely to fall as the diet period begins, and weight loss is likely.

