### **5. STATISTICAL PROCEDURES**

#### **5.1. Power Analysis**

##### **Power Analysis for Overall Study**

Sample size will be based on the change in postprandial metabolism (thermic effect of food) previously observed with a plant-based diet, compared with an active dietary control. The current power analysis assumes there will be a single t-test for the comparison of the changes in thermic effect of food observed in the two study groups, with an alpha level of 0.05.

In the prior study, the change at 14 weeks for the thermal effect of food was 4.7 with an SD of 12 in the intervention arm, and 0.3 with an SD of 9.4 in the control arm. Assuming that the true treatment effect is 4.4 kcal/170 min and that the SD of the change will be 12.0 units in the Diet Group and 9.4 units in the Control Group, as previously observed, the sample size required is 96 per arm (192 total) for 80% power, 109 per arm for 85% power, 128 per arm for 90% power.

However, if this magnitude of treatment effect is assumed to be present at the same magnitude of effect at each of the 5 evaluation points used in TEF assessment and assuming that the standard deviation is about 10.85 points for all observations, with 5 observations per participant, correlated at a magnitude of 0.7 with each other, the sample size required is 73 participants per arm (146 total) with 80% power, 83 per arm with 85% power, 98 per arm for 90% power.

Assuming an attrition of 10%, the required sample size is 81 per group, or 162 total for 80% power.

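### Section 5.3 names a multivariate ANCOVA as the main assessment of diet; if body weight is among its outcomes, expected weight loss could make it significant with no effect on TEF or insulin sensitivity

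*Protocol*

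**What the plan says.** Section 5.3 describes two analyses of the diet effect.

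- Baseline values of the key outcomes "will be included as covariates in the main assessments of the effect of diet in the multivariate analysis of covariance". The section does not say which outcomes form the dependent vector.
- "The initial test of the hypotheses will be examined by performing t-tests for independent samples on the difference score", that is, change from baseline. These tests have no baseline adjustment.

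The same section adds: "An alpha of 0.05 will be used for all statistical tests".

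Three other places bear on how to read this.

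- Section 1.2: "Changes in insulin sensitivity, postprandial metabolism, and body weight will be the primary dependent variables".
- Section 5.1, overall study: the sample-size calculation "assumes there will be a single t-test for the comparison of the changes in thermic effect of food".
- Section 4.2, on the Diet Group: "self-selected energy intake is likely to fall as the diet period begins, and weight loss is likely".

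In section 1.1, Aim 1 concerns a rise in TEF as a partial cause of weight change. Aim 2 concerns insulin sensitivity as the cause of that rise.

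**The concern.** A multivariate analysis of covariance on several outcomes has a joint null: the diet changes none of them. Rejection says that at least one outcome, or some linear combination, differs between groups. It does not say which.

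If body weight is in the vector, the protocol's own expectation of weight loss against an untreated control makes the joint null likely to be false whatever happens to TEF or insulin sensitivity. Section 2 names reduced energy intake as a separate route to weight loss, so weight loss without a TEF effect is a case this trial has to be able to recognise.

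What is at stake is the reading of the analysis that the protocol calls main. A significant joint p-value could be reported as the effect of diet while giving no evidence on either mechanism. The joint test is also not the test for which the trial was sized.

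**Working it through.** **1. The plan's own figures (section 5.1).** Inputs: difference 4.4; SDs of change 12.0 and 9.4; alpha 0.05, taken as two-sided; 80% power.

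Single t-test, normal approximation: n per arm = (1.960 + 0.842)² × (12.0² + 9.4²) / 4.4² = 7.85 × 232.36 / 19.36 = 94.2, so 95. The plan gives 96, which agrees within the small-sample correction.

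Five observations with SD 10.85 and correlation 0.7: the variance factor is (1 + 4 × 0.7)/5 = 0.76. Then n = 2 × 7.85 × 10.85² × 0.76 / 4.4² = 72.5, so 73, as stated. Both calculations concern TEF alone.

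**2. What the joint test would do.** Take the outcome vector to be the three variables of section 1.2, with their three baselines as covariates. Let the diet change weight only, by a standardised amount d = (difference in kg)/(SD of adjusted weight change), and let every pair of outcomes have correlation ρ. With n per arm, the group test is an F test on 3 and 2n − 2 − 3 − 3 + 1 degrees of freedom, with noncentrality

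λ = (n/2) × d² × (1 + ρ) / [(1 − ρ)(1 + 2ρ)].

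At n = 73 the degrees of freedom are 3 and 139, and the 5% critical value is 2.67.

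Weight differences come from section 2. The Diet Group lost 5.8 kg in the prior study, and the difference was 5.8 − 3.8 = 2.0 kg against an active diet. A 5.8 kg difference here supposes stable untreated controls; 3.0 kg is an intermediate value. The SD (3 to 6 kg) and ρ (0 to 0.5) are assumptions; the protocol gives neither.

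Worked ends of the 2.0 kg range at 73 per arm:

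- SD 6, ρ = 0: λ = 36.5 × (2/6)² = 4.06, rejection 35%.
- SD 3, ρ = 0.5: λ = 36.5 × (2/3)² × 1.5 = 24.3, rejection 99%.

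| Weight difference | 73 per arm | 120 per arm |
|---|---|---|
| 2.0 kg | 35–99% | 56–100% |
| 3.0 kg | 70–100% | 91–100% |
| 5.8 kg | 99.9–100% | 100% |

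The 120 per arm follows from the six cohorts of 40 in section 6.1 (240/2). All entries have zero true effect on TEF and insulin sensitivity.

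**3. Simulation check.** With 73 per arm, ρ = 0.3 and 2,000 runs per setting, the joint test rejected in 5% (d = 0), 76% (d = 0.5) and 100% (d = 1.16, i.e. 5.8 kg at SD 5). Separate ANCOVAs for the two outcomes with no effect rejected in 4.7% to 5.8% of runs, near the nominal 5%.

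**4. Power when only TEF moves.** At the 96 per arm that section 5.1 gives for SDs 12.0 and 9.4, d = 4.4/10.78 = 0.41. Assume a baseline–change correlation of −0.3 and ρ = 0.2. The adjusted d is 0.41/√(1 − 0.09) = 0.43. Power is about 72% for the joint test and 84% for a TEF-only ANCOVA.

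**The case against.** The strongest reply is that section 5.3 already contains outcome-specific tests. It ties the word hypotheses to change-score t-tests, and section 5.1 sizes the trial on such a test for TEF. Weight loss cannot make a t-test on TEF change significant. This stands, and it limits the harm. A reader might infer that the plan leaves TEF and insulin sensitivity without a test of their own; the documents do not support that. But the t-tests are called initial, they carry no baseline adjustment, and the label main goes to the multivariate analysis.

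Second, pooling the three outcomes is an inference. The text speaks of assessments in the plural and lists no dependent variables. The word multivariate may loosely mean covariate-adjusted, or may refer to repeated measurements of one outcome, such as the five TEF evaluation points in section 5.1. Under those readings the rejection rates above do not apply. This also stands. It makes the finding conditional, but the named method would then be the wrong name and the same edit would be needed.

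Third, an omnibus test is a legitimate procedure: the simulation shows that it holds its 5% level under its own null. The error would lie in reading it as evidence on TEF, which the protocol nowhere says it will do. That is fair, but the present wording does nothing to prevent it.

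**Conclusion.** The concern holds in conditional form. If the multivariate ANCOVA takes the three primary variables as its outcomes, its group test is not specific to either mechanism, and expected weight loss could make it significant with no effect on TEF or insulin sensitivity. This would be nearly certain for a 5.8 kg difference. For 2.0 kg the rate at 73 per arm is 35% to 99%, depending on the assumed SD and correlation.

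A reader might go further and say that weight loss alone is bound to make the main result significant. The documents do not support that: they give no SD of weight change, their only between-group figure is 2.0 kg, and they do not state that weight enters the same test as TEF. The loss of power (about 72% against 84% at 96 per arm) is secondary. It rests on assumed correlations and on weight not moving, which section 4.2 makes unlikely.

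**What to change.** In section 5.3, replace the multivariate analysis of covariance with a separate ANCOVA for each of TEF, insulin sensitivity and body weight: week-16 value on group, adjusted for that outcome's own baseline. State that each aim's conclusion about the between-group effect of diet rests on that outcome's own group coefficient and 95% CI. If a multivariate test is kept, label it a supportive omnibus test that cannot by itself support a claim about TEF or insulin sensitivity.

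The cost is a change of wording, with the same data and no more participants. The only loss is one omnibus p-value as the headline. Baseline adjustment should also gain a little over the plain t-test: at 96 per arm, about 84% against 80% power for TEF under the assumed baseline–change correlation of −0.3. The edit does not settle how alpha is shared across three primary variables, but the t-tests already planned raise that question equally.

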### **3.5. Group Assignment**

Participants will be told that, if accepted, they will be assigned either to a Diet Group or a Control Group. Accepted volunteers will be assigned to these groups using a computer-generated random-number table. Because assignment will be done simultaneously within each replication, allocation concealment is unnecessary.

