## **6. TIME LINE AND PARTICIPANT FLOW**

### **6.1. Time Line**

The study will be conducted in six cohorts, each including 40 participants, over a 3-year period.

For the first cohort, recruitment will take place October 2016 – January 2017. The intervention, including weekly meetings, will take place between February and May 2017 for a total of 16 weeks. For the second cohort, recruitment will take place in December 2016 and January, 2017. The intervention, including weekly meetings, will take place between March and July 2017. Similar time frames will apply in the two subsequent years.

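### Section 5.3 gives two analyses of the diet effect, an unadjusted t-test on change and a baseline-adjusted MANCOVA, without saying which decides; neither includes cohort.

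*Protocol*

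**What the plan says.** Protocol section 5.3 sets alpha at 0.05 for every test and describes the analysis of the diet effect in three places.

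- Adjusted analysis: "baseline values for key outcome variables will be included as covariates in the main assessments of the effect of diet". The model is a multivariate analysis of covariance, and the baseline values are the only covariates named.
- Unadjusted analysis: "The initial test of the hypotheses will be examined by performing t-tests for independent samples on the difference score", the score being the change from baseline.
- Choice of test, introduced for nutrient intake and physical measures: "If data are normally distributed, parametric tests for significant effects will be used; for non-normally distributed variables, non-parametric tests will be used". No particular non-parametric test is named.

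On assignment, section 3.5 says that "assignment will be done simultaneously within each replication" and gives no ratio, blocks or strata. Section 6.1 says: "The study will be conducted in six cohorts, each including 40 participants", over three years. No analysis in section 5 mentions cohort or replication.

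Section 5.1 first sizes the trial for a single t-test on change in the thermic effect of food (TEF). It then takes the final 81 per group from a calculation with five correlated observations per participant.

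**The concern.** The t-test is presented as the test of the hypotheses, and the MANCOVA as the main assessment of the same effect. The labels *initial* and *main* suggest a sequence, but they are not a decision rule. If one analysis gives p<0.05 and the other does not, the protocol does not settle whether the hypothesis is supported. Choosing after seeing both results raises the false-positive rate above 5%.

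The choice also affects power. If the t-test decides, baseline values that the trial collects anyway are used only by subtraction, which is less efficient than using them as a covariate. Leaving out cohort keeps any between-cohort variation in the error term.

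**Working it through.** **Inputs.** From section 5.1: TEF effect 4.4; SD of change 12.0 (Diet) and 9.4 (Control); 81 per group after a 10% attrition allowance. From section 6.1: six cohorts of 40. Assumed, because the protocol does not give them: baseline-to-week-16 correlation r of 0.5 to 0.7 (0.9 as a further case), equal variance at the two visits, the MANCOVA treated as a univariate ANCOVA of one outcome, and a cohort share of variance of 2% to 10%.

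**The plan's own figure.** The root-mean-square SD is √((12² + 9.4²)/2) = 10.78. A two-sided t-test at 0.05 (noncentral t) then needs 96, 109 and 128 per arm for 80%, 85% and 90% power, exactly as section 5.1 states.

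**How the two tests relate.** With variance σ² at each visit, the change has variance 2σ²(1 − r) and the ANCOVA residual has variance σ²(1 − r²). The ratio is (1 + r)/2, so ANCOVA scales the SD by √((1 + r)/2). Under the null hypothesis the two test statistics correlate at the same value, √((1 + r)/2).

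**Type I error and power.** The either-test error is the bivariate normal probability that at least one statistic exceeds 1.96 in absolute value. ANCOVA power uses SD 10.78 × √((1 + r)/2).

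| r | Correlation of statistics | Either test p<0.05 under the null | ANCOVA SD | ANCOVA power, 81 per arm | ANCOVA power, 108 per arm |
|---|---|---|---|---|---|
| 0.5 | 0.866 | 7.3% | 9.33 | 85% | 93% |
| 0.7 | 0.922 | 6.8% | 9.94 | 80% | 90% |
| 0.9 | 0.975 | 6.0% | 10.51 | 75% | 87% |

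The change-score t-test has 73% power at 81 per arm and 85% at 108 per arm. A simulation with 81 per arm and 6,000 runs gave either-test errors of 7.6% at r = 0.5 and 6.8% at r = 0.7, in agreement with the table.

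The protocol does not state 108 per arm. It follows from six full cohorts: 6 × 40 = 240, less 10% = 216, split equally. The 81-per-arm column treats all 81 as analysed. With only the 73 that section 5.1 expects to remain, the t-test has 69% power.

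**Cohort.** If cohort explains a share R² of the variance and allocation is balanced within cohort, the unadjusted standard error is too wide by 1/√(1 − R²). That factor is 1.010, 1.026 and 1.054 for R² of 2%, 5% and 10%. A simulation (six cohorts, 20 per arm in each, 20,000 runs) gave the following:

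| Cohort share of variance | Type I error without cohort | Type I error with cohort | Power without cohort | Power with cohort |
|---|---|---|---|---|
| 0% | 5.0% | 5.0% | 88% | 88% |
| 5% | 4.5% | 5.0% | 89% | 90% |
| 10% | 4.0% | 4.9% | 90% | 91% |

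**The case against.** **Baseline adjustment is already planned.** This is correct. Section 5.3 puts baseline values into the MANCOVA whatever the baseline comparison shows. A reader might infer that the plan throws baseline information away, but the text does not support that. The power loss arises only if the t-test decides, which is the question left open.

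**There are not three competing tests.** A reader might count the non-parametric test as a third chance of success. As written it replaces the parametric test, variable by variable, and does not add to it. Whether the switch reaches TEF or insulin sensitivity is also an inference, because it is introduced for nutrient intake and physical measures. The figures above therefore cover two tests only.

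**The calculation is not the stated model.** It treats a multivariate analysis as a univariate one and assumes equal variances. The error with the omnibus test is unknown and could be higher. A larger r makes both effects smaller, as the r = 0.9 row shows.

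**Cohort belongs in the SAP.** Covariate lists are often left there, and that replication means cohort is an inference, although it fits sections 3.5 and 6.1. A reader might also infer that omitting cohort makes the tests invalid. Under balanced allocation it makes them slightly conservative. This objection stands to the extent that the missing cohort term would not be a finding by itself.

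None of this removes the core point: the protocol itself names both an initial and a main analysis and gives no rule between them.

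**Conclusion.** The point holds in a limited form. Section 5.3 states two analyses of one effect at 0.05 and does not say which is confirmatory. Under the stated assumptions, a free choice between them costs about 2 percentage points of type I error (7.3% to 6.8% for r of 0.5 to 0.7, and 6.0% at 0.9).

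If the t-test decides, TEF power at 81 per group is 73%. ANCOVA gives 85% to 80% (75% at r = 0.9). At 108 per arm the comparison is 85% against 93% to 90%.

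Cohort is the smaller part: a standard error about 1% to 5% too wide for an assumed 2% to 10% of variance, with no inflation of type I error if allocation is balanced within cohort. These figures do not show that the planned analysis is invalid. They show that an unresolved choice can be closed, and some precision gained, from data the trial already collects.

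**What to change.** For each primary outcome, name one confirmatory analysis in section 5.3: an ANCOVA of the week-16 value (or the change) on arm, baseline value and cohort as a fixed factor. State that the change-score t-test and any non-parametric test are supportive, so that a normality test does not select the confirmatory analysis. Say in section 3.5 whether replication means cohort and whether allocation is balanced within it. Robust standard errors are optional.

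The cost is analysis wording and five degrees of freedom for six cohorts. No added participants, visits or measurements are needed.

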#### **Assessments of Physical Health, Weight, and Metabolism**

**General status, symptoms, and medication accounting.** Participants will be asked to report changes in their health and medication use.

**Height.** Height will be measured at baseline (only) with participants standing barefoot with their backs to a wall-mounted stadiometer and heels against the wall, recorded to the nearest 0.5 cm.

**Body weight.** With participants wearing light, indoor clothing but without shoes, body weight will be measured to the nearest 0.1 kg, using a digital scale. Body weight will also be assessed at each weekly group session for the Diet Group, but only data from weeks 0, 8, and 16 will be included in the analysis.

**Comprehensive Metabolic Panel.** These values will be evaluated at baseline only.

**Serum cholesterol and triacylglycerol concentrations and hemoglobin A1c** will be measured using standard methods.

The following measures will be assessed at weeks 0 and 16:

**Glucose Tolerance and Insulin Sensitivity.** An oral glucose tolerance test will be performed for three hours after an overnight fast. (Matsuda 1999) **Resting Energy Expenditure (REE).** Participants will be asked to report to the laboratory within 60 minutes of waking and after a 12-hour fast. Following 30 minutes of quiet rest in a dimly lit room, pulse, respiratory rate, and body temperature will be measured. REE will be measured for 20 minutes through indirect calorimetry (Cosmed Quark RMR, Chicago, IL) utilizing a ventilated hood system. The laboratory temperature will be maintained at 23 degrees C throughout, and precautions will be taken to minimize any disturbances that could affect the metabolic rate.

For premenopausal women, measures will be timed so as to occur in the luteal phase of the menstrual cycle.

**Postprandial metabolism** (thermic effect of food, TEF). After the REE determination, participants will be given a 720-kilocalorie test meal (Sustacal, Mead Johnson, Evansville, IN) to be ingested within 10 minutes. Metabolic rate will be measured in the same manner as above for 30 minutes at 2 and 4 hours postingestion.

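### Section 5.3 enters every missing week-16 TEF, insulin-sensitivity or body-composition value as an observed change of exactly zero, which biases the estimate if dropouts would have changed as completers did and overstates precision.

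*Protocol*

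**What the plan says.** Protocol Section 5.3 makes the initial test of the hypotheses from "t-tests for independent samples on the difference score denoting the change from baseline to the reporting period". Two sentences then deal with missing values. The general one is "For missing data in a reporting period, values from the previous period will be brought forward". The one for weight is "For body weight, drop-outs will be considered to have returned to baseline weights". The section states no other handling of missing data. It also plans a baseline-adjusted multivariate analysis of covariance, which would use the same filled-in values unless stated otherwise.

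The visit schedule decides what these sentences do. In Section 3.6, the line introducing glucose tolerance and insulin sensitivity, resting energy expenditure and TEF reads "The following measures will be assessed at weeks 0 and 16". Table 1 shows the same two time points for these measures and for body composition. Body weight differs: Section 3.6 says that "only data from weeks 0, 8, and 16 will be included in the analysis".

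**The concern.** For an outcome with only two visits, the previous period is baseline. Carrying it forward makes the change score exactly zero, and that zero goes into the t-test as if it had been measured. For body weight, dropouts reach the same zero through the return-to-baseline sentence. Only a participant who stays in the trial but misses week 16 could keep a week-8 weight, where one was taken. All three primary dependent variables named in Section 1.2 are therefore affected.

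An exact zero does not fit the protocol's own figures. Section 5.1 gives the comparison arm of the prior study a mean TEF change of "0.3 with an SD of 9.4 in the control arm": the mean hardly moved, yet individual changes scattered widely. Filling with zeros removes that scatter and counts unmeasured people in n. At stake are the size of the reported diet effect and the precision claimed for it.

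**Working it through.** **Inputs.**
- Diet arm (Section 5.1): "the change at 14 weeks for the thermal effect of food was 4.7 with an SD of 12 in the intervention arm".
- Control arm (Section 5.1): "0.3 with an SD of 9.4 in the control arm".
- True difference: 4.7 − 0.3 = 4.4 kcal/170 min.
- Test: "with an alpha level of 0.05". Sidedness is not stated; two-sided reproduces the plan's figures.
- Attrition: 10% (Section 5.1). The 20% rate used below is an assumed what-if; the documents do not give it.
- n per arm: 81 (Section 5.1), or 120 from Section 6.1 (six cohorts of 40 = 240, split equally).

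**The plan's own figures.** The pooled SD is √((12² + 9.4²)/2) = 10.78. A two-sided t-test then needs 96, 109 and 128 per arm for 80%, 85% and 90% power, as stated. With five observations correlated at 0.7, the SD is 10.85 × √((1 + 4 × 0.7)/5) = 9.46, which gives 73, 83 and 98, as stated. Attrition: 73/0.9 = 81.1, stated as 81.

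**Effect of zero-filling.** Let d be the dropout share in an arm, with dropouts' unobserved changes distributed like those of completers. The filled-in arm then has
- mean (1 − d)μ
- variance (1 − d)SD² + d(1 − d)μ²

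At d = 0.10 in both arms:
- Difference: 0.9 × 4.7 − 0.9 × 0.3 = 4.23 − 0.27 = 3.96.
- Diet variance: 0.9 × 144 + 0.09 × 22.09 = 131.59.
- Control variance: 0.9 × 88.36 + 0.09 × 0.09 = 79.53.
- Zero-filled SE at 81 per arm: √(211.12/81) = 1.61.
- Observed-data SE: √(232.36/72.9) = 1.79.
- Complete-data SE: √(232.36/81) = 1.69.

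The same formulas give:

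| n per arm | Dropout, both arms | Difference | SE zero-filled | SE observed data | SE complete data | 95% coverage of 4.4 |
|---|---|---|---|---|---|---|
| 81 | 10% | 3.96 | 1.61 | 1.79 | 1.69 | about 94% |
| 120 | 10% | 3.96 | 1.33 | 1.47 | 1.39 | about 94% |
| 81 | 20% (assumed) | 3.52 | 1.53 | 1.89 | 1.69 | about 91% |
| 120 | 20% (assumed) | 3.52 | 1.26 | 1.56 | 1.39 | about 89% |

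At 10% dropout the zero-filled SE is about 10% below the observed-data SE and about 5% below the complete-data SE. A simulation of 100,000 trials at 81 per arm agrees: mean difference 3.97, mean SE 1.61 and coverage 94.2% at 10% dropout; coverage 91.1% at 20%.

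**Unequal dropout.**
- 15% diet, 5% control: 0.85 × 4.7 − 0.95 × 0.3 = 3.71.
- 5% diet, 15% control: 0.95 × 4.7 − 0.85 × 0.3 = 4.21.

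The estimate depends on which arm loses people.

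**Power.** Taking power as Φ(difference/SE − 1.96), at 81 per arm and 10% dropout the single t-test has 68.9% zero-filled against 69.3% on observed data. With the five-observation SD the figures are 80.2% and 80.7%.

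**The case against.** The strongest objection is that the bias is conditional. If people who leave the diet go back to where they started, as Section 5.3 assumes for weight, the mean difference among all randomised participants is itself near 0.9 × 4.4 = 3.96, and zero-filling is centred about right. This stands: the documents do not settle what dropouts' values would have been. But Section 5.3 gives no reason for assuming reversion for TEF or insulin sensitivity, and zero-filling treats that assumption as known data. For weight, return-to-baseline is a deliberate, pre-stated and usually conservative choice, and it deserves to stay in the report.

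Four stronger readings are tempting, and the documents do not support them.

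- A reader might infer that Sections 5.1 and 5.3 contradict each other, because the sample size is inflated for attrition while dropouts are kept in the analysis. They do not. Zero-filling dilutes the effect, so it needs inflation too, and by nearly the same amount, as the power figures show.
- A reader might infer that the test is invalid or loses power. With equal dropout and no true difference, both arm means shrink alike and the test keeps its size; power is almost unchanged.
- A reader might take 89% as the expected coverage. It needs 20% dropout and 120 per arm. At the protocol's own 10%, coverage is about 94%.
- A reader might infer that the rule always shrinks the effect and the SE. With an assumed control change of +2 and dropout of 2% diet and 30% control, a true 2.70 becomes 0.98 × 4.7 − 0.70 × 2 = 3.21. For weight no SD of change is given. Taking the 5.8 kg loss from Section 2, no control change and 10% dropout, the SE is 3.4% above the complete-data SE at an assumed SD of 3 kg and 0.3% to 3.9% below it at 4 to 8 kg.

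**Conclusion.** The point holds as a fault of estimation. For TEF, insulin sensitivity and body composition, the stated rule records every missing week-16 value as an observed change of zero. If dropouts would have changed as completers did, 10% attrition in both arms moves the expected TEF difference from 4.40 to 3.96. The SE falls to 1.61 against 1.79 at 81 per arm, or 1.33 against 1.47 at 120 per arm. The loss of coverage is small at 10% and grows with dropout. Section 5.3 itself plans to compare dropout between arms, and only the Diet Group has weekly classes (Section 4.2), so unequal dropout is a realistic case; the result would then depend partly on who left. These sizes are for TEF only, since the protocol gives no SD of change for insulin sensitivity, body composition or weight. The rule should be changed, but it does not by itself invalidate the trial's test.

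**What to change.** For TEF, insulin sensitivity and the other outcomes measured at weeks 0 and 16, replace the carry-forward sentence in Section 5.3. Use either a likelihood-based model of the baseline and week-16 values of all randomised participants, or ANCOVA with multiple imputation by arm. Keep the zero-change (baseline-carried) analysis as a stated sensitivity analysis for all three primary outcomes, including TEF and insulin sensitivity. For body weight, report the same model alongside the pre-stated return-to-baseline analysis.

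The cost is a change of analysis wording and a little programming; no visit, procedure or participant number changes. The downside is that the main analysis then assumes data are missing at random. That assumption becomes explicit, and the retained zero-change analysis probes it.
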